### Safety assessments

All co-existing diseases or conditions related to the intervention will be treated in accordance with prevailing medical practice and will be reported as an adverse event. In cases where the functional and cognitive state of a participant decreases due to an adverse event (e.g. illness, falls, etc.) the program will be individualized and adapted for that person upon her/his return.

### Power and sample size

Sample size for the current study was calculated to detect a significant clinical difference on the dual-task gait speed test [54]. Accepting an alpha risk of 0.05 and a beta risk of 0.20 in a bilateral contrast, 141 individuals are required to detect a difference equal to or greater than 0.08 m/seg in the dual-task gait speed test (SD = 0.24). The sample size was increased by 20% to account for losses during follow-up and an additional 5% for mortality. The resulting sample size is 188 individuals, allocating 94 participants to each group.

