**Methods:**

This multicenter randomized controlled trial will include 188 participants who will be randomly allocated to either a multicomponent exercise program or to the same multicomponent program with simultaneous cognitive training (dual-task training). Inclusion criteria are as follows: ≥ 70 years, ≥ 50 on the Barthel Index, ≥ 20 on the Mini Examen Cognoscitivo (MEC-35) who are able to stand up and walk independently for 10 m. Subjects in the multicomponent group will attend a twice-a-week multicomponent exercise program of 1-h duration per session, consisting of strength and balance exercises. Participants in the dual-task group will perform the same multicomponent exercise program with concurrent individually tailored cognitive tasks. Study assessments will be conducted at baseline and at 3 months. The primary outcome measure will be gait speed under dual-task conditions and secondary outcomes will include physical fitness measurements, gait spatiotemporal parameters, cognition and emotional assessments, several frailty scales and objectively measured physical activity.

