Dual-task performance can be modified with specific dual-task training [22, 23]. In fact, this type of intervention can maintain or even improve cognitive function [24, 25], especially executive function [26]. Two models have been suggested that might explain training-mediated dual-task performance changes [27]. The task-automatization model is based on the assumption that individual tasks can be automatized and predicts similar improvements either with single-task or dual-task training [27]. Alternatively, the task-integration model advocates for the efficient integration of both tasks through dual-task training, resulting in dual-task performance improvements [27]. According to the latter model, dual-task performance would only improve after dual-task but not single-task training. Furthermore, dual-task training may be superior to single-task training [28–30], since dual-task training requires greater cognitive and motor resources and is more complex in terms of control and coordination demands. Pellecchia et al. [31] observed greater improvements in postural sway under dual-task conditions after dual-task training compared to single-task training, supporting the task-integration model and suggesting that both physical and cognitive functions interact in a way still to be revealed.

To our knowledge, no studies have explored the effects of a supervised dual-task multicomponent exercise intervention in long-term nursing home facilities from a broad perspective of frailty, assessing functional capacity under single-task and dual-task conditions, physical activity, cognitive performance and emotional status. Therefore, we designed a randomized multicenter study, the Aging-ON_DUAL-TASK_ study, to test hypothesis that the addition of cognitive training to a supervised multicomponent exercise program can improve gait speed performance under dual-task conditions by, at least 0.08 m/seg in a population of older adults in long-term nursing homes. The major aim of the Aging-ON_DUAL-TASK_ study is to determine if a supervised dual-task program carried out in long-term nursing homes can attenuate frailty to a greater extent than the same multicomponent exercise program without cognitive training.

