### Inclusion and exclusion criteria, recruitment, and randomization

The inclusion criteria, recruitment, and randomization methodologies in the Aging-ON_DUAL-TASK_ study will be the same as on a previously published protocol [33]. The inclusion criteria will be: age ≥ 70 years old; a Barthel Index [34] score ≥ 50 and score ≥ 20 on the MEC-35 Test [35] [Mini-examen cognoscitivo, an adapted and validated version of Mini Mental State Examination (MMSE) in Spanish]; and capacity to stand up and walk independently for at least 10 m. Participants will not be eligible if they are judged clinically unstable by the medical staff, or have in any other condition in which entering the study would not be in the subject’s best interests.

Identification of individuals that meet the inclusion criteria will be facilitated by the databases of the included long-term nursing homes. The primary recruitment strategy will be information provided to the potential participants by the medical and nursing professionals from each facility. All volunteers will receive detailed study information at their reference sites through the research team: objectives, measurement variables, and other details about the interventions will be explained orally and in writing to both potential participants and their families. After signing the informed consent, the participants within each center will randomly be assigned (in a 1:1 ratio) through sealed opaque envelopes to either the multicomponent or the dual-task group by coin-tossing sequence generation.

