### Statistical considerations

Data analysis will be performed using the IBM SPSS Statistics 24 statistical software package (SPSS, Inc., Chicago, IL). Intention-to-treat analyses will be performed and the level of statistical significance will be set at *p* < .05 for all computations. First, all data will be checked for normality of distribution using the Kolmogorov-Smirnov test. Results will be expressed as mean (with standard deviation) for continuous and normally distributed variables and as median (with interquartile range) when normality of data for that variable cannot be assumed. In the case of categorical variables, frequency counts and percentages will be used to describe the results. Tests for baseline comparisons will be selected based on the nature and distribution of the data: Student’s-t test with continuous and normally distributed variables, Mann-Whitney test with non-normally distributed continuous variables, and Chi-squared test with categorical variables.

To test the effects of training interventions, mixed-designed ANCOVA-s or the Friedman test, including baseline measurements, age, or gender as covariates, will be performed for physical, cognitive, and emotional variables. In cases where a significant F value is found, LSD post hoc procedures will be performed for pairwise comparisons.

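### The stated inputs require 141 participants per group, but the plan uses 141 as the trial total, so unadjusted power for 0.08 m/s is about 50% at the planned evaluable size, not 80%

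*Protocol article*

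**What the plan says.** The Protocol article, under Power and sample size, gives all the inputs. The error rates are "Accepting an alpha risk of 0.05 and a beta risk of 0.20 in a bilateral contrast". The requirement follows: "141 individuals are required to detect a difference equal to or greater than 0.08 m/seg in the dual-task gait speed test (SD = 0.24". Losses are then added: "The sample size was increased by 20% to account for losses during follow-up and an additional 5% for mortality". The result is "The resulting sample size is 188 individuals, allocating 94 participants to each group". The Abstract (Methods) repeats 188 as the size of the whole trial: "This multicenter randomized controlled trial will include 188 participants who will be randomly allocated".

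The Introduction says what the 0.08 m/s stands for. The hypothesis is that "the addition of cognitive training to a supervised multicomponent exercise program can improve gait speed performance under dual-task conditions by, at least 0.08 m/seg". Both arms receive the exercise programme, so this is a difference between arms.

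**The concern.** A difference of one third of a standard deviation (0.08/0.24) is modest, and 141 participants over two arms is few for 80% power to detect it. The number coincides with the usual per-group requirement for these inputs, yet the plan carries it forward as a total.

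This calculation is the only stated basis for the size of the trial, and it concerns the primary outcome. A reader will take it that a true benefit of 0.08 m/s has a 20% chance of being missed. If the real chance is nearer one half, a null result says little, but it would be read as evidence against adding cognitive training.

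**Working it through.** **Inputs.** From Power and sample size: two-sided alpha 0.05, power 0.80, difference 0.08 m/s, SD 0.24, losses 20% + 5%. From the randomization section: participants will "randomly be assigned (in a 1:1 ratio", so the arms are equal.

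**Reproducing 141.** For two independent means with equal arms:

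n per group = 2 × (z₀.₉₇₅ + z₀.₈₀)² × (SD/difference)² = 2 × (1.960 + 0.842)² × (0.24/0.08)² = 2 × 7.849 × 9 = 141.3

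The t-test version gives 142.2. The figure of 141 therefore reproduces as a per-group number. As a total it does not, because the total required is about 282.

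**How the plan uses 141.** 141/(1 − 0.25) = 188 and 188/2 = 94. Both printed results follow exactly if 141 is the total for both arms. The allowance for losses is arithmetically sound. The number it was applied to is not.

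**Power the design delivers (unadjusted, SD 0.24).**

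- 141 evaluable, 70.5 per arm: standard error = 0.24 × √(2/70.5) = 0.0404. 0.08/0.0404 = 1.979, and 1.979 − 1.960 = 0.019, so power is 50.8% (t-test 50.2%).
- 188 evaluable, 94 per arm: standard error = 0.24 × √(2/94) = 0.0350. 0.08/0.0350 = 2.285, and 2.285 − 1.960 = 0.325, so power is 62.8% (t-test 62.3%).
- 141 per arm: 79.9% (t-test 79.7%), which is the power the plan claims.

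**Difference detectable with 80% power.** 2.802 × 0.0404 = 0.113 m/s with 141 evaluable (t-test 0.114). 2.802 × 0.0350 = 0.098 m/s with 188 evaluable (t-test 0.099).

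**What the stated inputs imply.** 2 × 141 = 282 evaluable and 282/0.75 = 376 randomised, twice the planned number.

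**Sensitivity to baseline adjustment.** Suppose that 0.24 is the SD of gait speed at one time point and that r is the correlation between baseline and 3 months. ANCOVA then reduces the variance by the factor (1 − r²). The documents give no value of r, so these rows are assumptions (normal approximation):

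| r | Power, 141 evaluable | Power, 188 evaluable |
|---|---|---|
| 0 | 51% | 63% |
| 0.3 | 55% | 67% |
| 0.5 | 63% | 75% |
| 0.6 | 70% | 82% |
| 0.7 | 79% | 89% |
| 0.8 | 91% | 97% |

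With 141 evaluable, 80% requires 1 − r² = 70.5/141.3 = 0.499, so r is about 0.71.

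**The case against.** The strongest reply is that the planned analysis is not an unadjusted comparison. Statistical considerations names "mixed-designed ANCOVA-s or the Friedman test, including baseline measurements, age, or gender as covariates". If 0.24 is a cross-sectional SD and the correlation is high, actual power could reach 80%. This stands as a limit on the conclusion: the 50% describes the stated inputs without adjustment and after the full 25% loss, and power under the planned model is unknown. It does not restore the claim, because the sample-size paragraph states no correlation and applies no reduction. The wording of the analysis section also leaves baseline adjustment optional, and the Friedman test named there takes no covariates.

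A related point concerns the SD. The paragraph does not say whether 0.24 refers to the 3-month value or to the change from baseline. If it is the SD of whichever quantity is analysed, the formula and the answer are the same. If it is cross-sectional and change is analysed, the relevant SD is 0.24 × √(2(1 − r)). That falls to 0.17, enough for 80% with 141 evaluable, only at r = 0.75, and for r below 0.5 it exceeds 0.24 and power drops below 50%.

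The total of 141 can also be matched another way. A paired or one-sample formula gives (1.960 + 0.842)² × 9 = 70.6 per group, or 141.3 over two groups. How the number arose is therefore an inference. But that formula tests change within an arm, not the difference between arms that the Introduction sets as the hypothesis, so the total remains unsupported. A one-sided test does not help either: it needs 112 per group, and the protocol specifies a two-sided one.

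**Conclusion.** The concern holds. On the protocol's own inputs, 141 is the number needed in each group, and the plan uses it for both groups together. Unadjusted power for a true 0.08 m/s difference is about 50% at the planned evaluable size and about 62% with no losses at all, against the 80% claimed. These figures assume that 0.24 is the SD of the analysed quantity and that no covariate reduces it. Adjustment for baseline could close the gap if the correlation is about 0.71 or higher, but nothing in the document establishes that. All the figures needed are printed and they disagree with each other, so this is an error in the paragraph and not a detail left to a fuller document.

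**What to change.** Rewrite the sample-size paragraph in one of two ways.

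1. Keep the calculation and correct its meaning. Say that 141 is the requirement per group and, in the same place, what 188 randomised delivers: about 50% power for 0.08 m/s with 141 evaluable, unadjusted, or 80% power for about 0.114 m/s. The first statement without the second would print a requirement that 94 per arm cannot meet.
2. Re-derive the power of 188 on the baseline-adjusted ANCOVA. State whether 0.24 is a cross-sectional or a change SD, give the assumed correlation and its source, and show power for r from 0.5 to 0.8. The correlation should come from data, such as the pilot if it measured dual-task gait speed at both time points. It should not be set at 0.71 because that value returns 188.

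In either case, make the baseline value a mandatory covariate in the primary model, since this is the cheapest gain in power available.

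The cost is protocol wording and a less favourable stated power or detectable difference. No extra enrolment is needed for the correction. Keeping 80% unadjusted power for 0.08 m/s would instead mean about 376 randomised, and the Discussion already expects difficulty in reaching the present target.

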### Statistical considerations

Data analysis will be performed using the IBM SPSS Statistics 24 statistical software package (SPSS, Inc., Chicago, IL). Intention-to-treat analyses will be performed and the level of statistical significance will be set at *p* < .05 for all computations. First, all data will be checked for normality of distribution using the Kolmogorov-Smirnov test. Results will be expressed as mean (with standard deviation) for continuous and normally distributed variables and as median (with interquartile range) when normality of data for that variable cannot be assumed. In the case of categorical variables, frequency counts and percentages will be used to describe the results. Tests for baseline comparisons will be selected based on the nature and distribution of the data: Student’s-t test with continuous and normally distributed variables, Mann-Whitney test with non-normally distributed continuous variables, and Chi-squared test with categorical variables.

To test the effects of training interventions, mixed-designed ANCOVA-s or the Friedman test, including baseline measurements, age, or gender as covariates, will be performed for physical, cognitive, and emotional variables. In cases where a significant F value is found, LSD post hoc procedures will be performed for pairwise comparisons.

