## Methods

### Study design and participants

Based on the proposed objective, an experimental multicentre simple randomized study was designed (Aging-ON_DUAL-TASK_). Participants will be randomly allocated to either a multicomponent exercise program or to the same multicomponent program with simultaneous cognitive training (dual-task program). Participants will be recruited from eight long-term nursing homes in Gipuzkoa, Basque Country, Spain. Each site will enroll a minimum of 16 subjects and interventions will take place between June 2018 and December 2018. Researchers responsible for data gathering will be blinded to group assignment. The assessments will be carried out by research staff at baseline and at 3 months after the beginning of the intervention. The study has been designed and results will be reported following the CONSORT Statement extension for trials of non-pharmacological interventions and pragmatic intervention trials (Fig. 1).

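### The Friedman test, named as an alternative for testing the training effect, cannot compare the two arms and cannot take the covariates listed for it

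*Protocol article*

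**What the plan says.** The question is a comparison between arms. The Introduction asks whether the dual-task program "can attenuate frailty to a greater extent than the same multicomponent exercise program without cognitive training". Under Study design and participants there are two randomised arms, and assessments take place "at baseline and at 3 months after the beginning of the intervention", so each outcome has two measurements per participant.

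The Statistical considerations section opens its testing paragraph with "To test the effects of training interventions" and then names "mixed-designed ANCOVA-s or the Friedman test, including baseline measurements, age, or gender as covariates", for the physical, cognitive and emotional variables alike. It does not say when one test is used and when the other.

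The paragraph before it says "all data will be checked for normality of distribution using the Kolmogorov-Smirnov test". It links the result to the choice between mean and median. It then adds "Tests for baseline comparisons will be selected based on the nature and distribution of the data" and lists Student's t, Mann-Whitney and chi-squared. Mann-Whitney, the only rank test between groups in the section, is therefore assigned to baseline comparisons and not to outcomes.

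**The concern.** The Friedman test ranks the repeated measurements inside each participant and asks whether the occasions differ. Arm does not enter the calculation, and neither can baseline, age or gender. The sentence therefore gives a between-arm question to a test that cannot address it, and describes an adjustment that the test cannot make.

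This matters in this trial because both arms exercise, and the Discussion reports that physical performance improved in both pilot groups. A shared improvement over time is the expected result. Friedman would detect that improvement, and the plan would label it an effect of the training interventions.

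**Working it through.** **Inputs.**
- SD of dual-task gait speed 0.24 m/s and target difference 0.08 m/s (Power and sample size).
- Two-sided alpha 0.05 (same section).
- Evaluable number: 188 × (1 − 0.25) = 141, or about 70 per arm.
- Two visits (Study design and participants).
- Assumed, because the protocol does not give them: normal data, a baseline-to-3-month correlation r of 0.7 (range 0.5 to 0.8), and the size of the gain in each arm.

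The protocol states no operating figure for this test, so there is none to reproduce.

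**Step 1. What Friedman becomes with two visits.** Let n+ and n− be the numbers of participants who rise and fall, and n their sum. The statistic is (n+ − n−)² / n, referred to chi-square on 1 degree of freedom, which is the sign test. It depends only on the direction of each participant's change. Shuffling the arm labels leaves it unchanged, so it carries no information about the arm effect.

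**Step 2. Equal gains of 0.05 m/s in both arms (true difference between arms zero), r = 0.7.**
- SD of change = 0.24 × √(2 × (1 − 0.7)) = 0.186.
- Probability that a participant rises = Φ(0.05 / 0.186) = 0.606.
- With n = 140, the test rejects when n+ is at least 82 or at most 58 (82 gives 24² / 140 = 4.11, above 3.84; 81 gives 3.46).
- The exact binomial probability of rejection is 72%. Simulation gives 72% to 74%.
- ANCOVA of the 3-month value on arm and baseline rejects in about 5%, the nominal level.

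At r = 0.5 and 0.8 the Friedman figure is about 50% and 88%, and ANCOVA stays near 5%.

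**Step 3. Friedman run separately in each arm, same scenario.** Each arm is significant with probability 0.40, so exactly one arm is significant in 2 × 0.40 × 0.60 = 48% of trials (simulation 47% to 50%). This is still two tests of time. It also invites a claim of superiority from one significant and one non-significant p-value.

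**Step 4. A true difference of 0.08 m/s between arms, r = 0.7.**

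| Gains (multicomponent, dual-task) | Friedman rejects | ANCOVA rejects |
|---|---|---|
| −0.04, +0.04 | about 5% | about 79% |
| +0.05, +0.13 | over 99% | about 79% |

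The between-arm difference is the same in both rows. Friedman goes from its nominal level to near certainty because only the average change over time has moved.

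**Step 5. What the figures do not show.** Steps 2 to 4 assume that Friedman is used. Suppose instead that a Kolmogorov-Smirnov test with Lilliefors correction at 0.05 made the choice. In the setting of Step 2, with normal data, it sent 4% of trials to Friedman when the 3-month value was tested, and 7% when either visit was tested. The false-positive rate of the whole procedure was then 7% to 10%. Skewed outcomes would take the Friedman route more often, but none was simulated.

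**The case against.** The strongest reply is that ANCOVA is named first, is a valid between-arm method and may serve most outcomes, including the primary one. Nothing in the protocol suggests that dual-task gait speed is non-normal, and the sample size treats it as a mean with an SD. The 72% therefore describes a branch, not the trial. This stands, and the figure should be quoted only as conditional on Friedman being used.

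A reader might also infer that the Kolmogorov-Smirnov check on raw variables decides which hypothesis is tested, and object to that as a second error. The documents do not support this as a stated rule. The check is tied to descriptive statistics and, through the mention of distribution, to the baseline tests. Between ANCOVA and Friedman the text says only "or". Use for non-normal outcomes is the likely reading of the section, but it is an inference.

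A third tempting claim is that Friedman would miss real differences. The 5% row in Step 4 needs one arm to worsen by as much as the other gains, whereas both arms are expected to improve. With gains of 0.05 and 0.13 Friedman rejects almost always, though for the wrong reason.

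The objection does not remove the core point. An article may leave detail to a fuller plan, but here it names a specific test for the training effect and attaches covariates that the test cannot take. More detail elsewhere would not make that sentence right.

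**Conclusion.** The concern holds as a defect in one named branch of the analysis. Friedman cannot compare dual-task with multicomponent training and cannot adjust for baseline, age or gender. No other sentence repairs this, because no between-arm rank method is named for outcomes. That conclusion follows from the form of the test and needs no assumption about the data.

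The size is conditional: if Friedman is used, equal gains of 0.05 m/s give about 72% rejections at r = 0.7 (about 50% to 88% for r from 0.5 to 0.8), against 5% for ANCOVA. It rests on 70 evaluable participants per arm, SD 0.24, normal data, and an assumed gain and correlation. The protocol does not support reading 72% as the false-positive rate of the trial, or saying that the primary outcome will be analysed by Friedman.

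**What to change.** Delete the Friedman test from the sentence on training effects. In its place, name one between-arm method for outcomes where the ANCOVA assumptions are doubtful, comparing 3-month values between arms with adjustment for baseline. Rank ANCOVA (Quade) or ANCOVA with robust or bootstrap standard errors would each serve. Any pre-named method that compares the arms and keeps the baseline adjustment meets the point. State in the same sentence when it replaces the standard ANCOVA.

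The cost is one sentence. No new data, visits or participants are needed.

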## Discussion

The current trial is a large multi-center randomized study aiming to investigate whether dual-task performance, including gait and cognitive parameters, can be improved by specific dual-task training. So far, guidelines for the geriatric population and professionals working in the field are scarce, despite the exponentially increasing number of people above 65 years old. Older adults in long-term nursing homes are at particular risk of adverse outcomes and have been the focus of interventions aiming to prevent or reverse frailty [55].

The results of the present study will add valuable knowledge about the effects of the dual-task program in long-term nursing home residents, taking together functional, cognitive, and emotional variables linked to frailty. Particularly, analysis of a multicomponent exercise program and the same program with simultaneous cognitive training, or dual-task, will help us to design interventions to improve or at least maintain functionality and cognition in long-term nursing home residents.

One of our main concerns at the time of designing the dual-task intervention was the fact that when performing a dual-task exercise, the execution velocity of the physical task could be reduced when compared with a single task exercise. In addition, movement technique could also be altered if compared to single task training. Consequently, we feared that a dual-task program might affect physical performance and hence not improve physical parameters to the same extent as the multicomponent program. Thus, we conducted a pilot study to ascertain if both the multicomponent and the dual-task programs produce similar training adaptations, in which we successfully observed significant physical improvements in both groups [56].

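### Unadjusted LSD tests follow an unnamed significant F, so within-arm before-after results may be read as a difference between the arms

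*Protocol article*

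**What the plan says.** The Introduction frames a between-arm question. It hypothesises that adding cognitive training improves dual-task gait speed by at least 0.08 m/s, and it aims to show that frailty is attenuated more than by the multicomponent programme alone. Participants are randomised 1:1 to two arms and assessed at baseline and 3 months.

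For training effects, Statistical considerations plans mixed-design ANCOVAs (or a Friedman test), with baseline measurements, age or gender as covariates. It then adds: "In cases where a significant F value is found, LSD post hoc procedures will be performed for pairwise comparisons". On the error level it says that "the level of statistical significance will be set at *p* < .05 for all computations".

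The section does not name the F that opens the post hoc step, the pairs to be compared, or the result that answers the between-arm question.

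**The concern.** A mixed-design model with two arms and two visits gives three F tests: arm, time and arm-by-time. Each has one degree of freedom, so a significant main effect is already a single comparison and LSD adds nothing to it. The pairwise tests that do add something are arm against arm at each visit, baseline included, and baseline against 3 months within each arm.

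The within-arm tests are the problem. Both arms receive supervised exercise, so a significant time effect is likely even if cognitive training adds nothing. Read literally, the rule then permits a before-after test in each arm at the .05 level without adjustment. If dual-task is significant and multicomponent is not, that pattern is easily reported as superiority. It is not evidence that the arms differ, because no test has compared them.

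**Working it through.** **Plan's own figure.** The article gives no error rate for the post hoc rule, so there is nothing to reproduce on this point.

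**Inputs from the article.** Two arms and two visits; every test at .05; SD 0.24 m/s; 94 participants per arm (Power and sample size: "The resulting sample size is 188 individuals, allocating 94 participants to each group").

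**Assumptions, not in the article.** The true change is equal in both arms; the SD is 0.24 at both visits; the baseline-to-3-month correlation r lies between 0.5 and 0.9; the within-arm test is a simple before-after comparison without covariates.

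**Step 1, no gate.** Let p be the power of the before-after test within one arm. With equal true change and independent arms, P(exactly one arm significant) = 2p(1 − p). The maximum is 2 × 0.5 × 0.5 = 50%, at p = 0.50.

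**Step 2, add the F gate.** Let a and b be the within-arm z statistics for dual-task and multicomponent, independent with a common mean. The time test is (a + b)/√2 and the arm-by-time test is (a − b)/√2, each compared with 1.96. From 2,000,000 simulated draws per row, the probability that the gate opens and exactly one arm is significant is:

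| Within-arm power p | No gate, 2p(1 − p) | Gate: time F | Of which favours dual-task | Gate: arm-by-time F |
|---|---|---|---|---|
| 0.05 (no change) | 9.5% | 3.2% | 1.6% | 3.1% |
| 0.50 | 50.0% | 45.6% | 22.8% | 4.9% |
| 0.56 | 49.4% | 46.0% | 23.0% | 4.9% |
| 0.80 | 32.0% | 31.5% | 15.8% | 4.3% |
| 0.90 | 18.0% | 18.0% | 9.0% | 3.5% |

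If either the time or the arm-by-time F opens the gate, the maximum is about 47%. At p = 0.50 that figure is 46.6%. The overlap of the two gates is therefore 45.6 + 4.9 − 46.6 = 3.9%, and 45.6 − 3.9 = about 42% of trials show the pattern after a significant time F while the arm-by-time F is not significant.

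**Step 3, where the peak falls.** The SD of change is 0.24 × √(2(1 − r)), and p = 0.50 needs a true gain of 1.96 × SD of change/√94.
- r = 0.5: 1.96 × 0.240/9.70 = 0.049 m/s.
- r = 0.9: 1.96 × 0.107/9.70 = 0.022 m/s.

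If both arms instead gain 0.08 m/s, p is 0.90 at r = 0.5, so 2p(1 − p) is about 18%. At r = 0.7, p is 0.987 and the figure is about 3%. With about 70 evaluable per arm, the same gain gives 32% and 10%.

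**Step 4, the contrast that answers the question.** Write Y0 and Y1 for baseline and 3 months. Regressing Y1 on arm and Y0 is the usual ANCOVA. Regressing Y1 − Y0 on arm and Y0 only subtracts 1 from the Y0 coefficient, so the arm estimate and p-value are unchanged. The arm-by-time test therefore equals the ANCOVA when baseline is also a covariate. Its type I error is 5%.

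**The case against.** The strongest reply is that the section never mentions before-after tests within arms. It introduces the models as tests of the training interventions, and the aim and the 0.08 m/s target are both comparisons between arms. Reading the F as arm-by-time is equally open, and the misleading pattern is then rare. A condensed article may also leave the choice of contrast to a fuller plan.

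Much of this stands, and it rules out several stronger readings that a reader might infer:
- **That the trial will judge efficacy from within-arm significance.** The text permits this but does not say it.
- **That the risk is 50%.** That is the ungated maximum. It omits the F gate, counts both directions and needs within-arm power of one half.
- **That the arm main effect has very low power.** Without baseline adjustment, and assuming 70.5 per arm and r = 0.7, power for a true 0.08 m/s is about 19%. But baseline is among the listed covariates. Once it is included, the main effect has the ANCOVA p-value, and only the estimate is halved.
- **That the Discussion shows the authors will reason this way.** The remark that a pilot was one "in which we successfully observed significant physical improvements in both groups" concerns earlier work and a different worry, that dual-tasking might blunt physical gains. It does not govern this analysis.

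The appeal to omitted detail does not remove the point. The article states a positive decision rule, any significant F followed by unadjusted pairwise tests, and that rule does not fit a two-arm, two-visit design.

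**Conclusion.** The point holds as a badly fixed decision rule. Two permitted readings of one sentence give very different chances of a misleading pattern when the arms are equal: up to about 46% if a significant time F opens the LSD tests, about 23% favouring dual-task, against at most 4.9% if the arm-by-time F does. The upper figure is a peak near 50% within-arm power; it falls to about 31% at 80% and 18% at 90%. Where this trial would lie cannot be fixed, because within-arm power depends on the true gain and on the baseline-to-3-month correlation, and the article gives neither. The percentages also rest on equal true change in both arms and a normal approximation. They describe how often the pattern would appear, not how often the authors would misread it.

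**What to change.** State that the treatment effect for each continuous outcome is the between-arm difference at 3 months with a 95% confidence interval, from an ANCOVA that always includes the baseline value of that outcome. The current list, joined by an or, leaves it unclear whether baseline always enters. The arm-by-time test may be named instead, provided baseline is also a covariate. Remove the F gate and the LSD step as a basis for conclusions, and label within-arm changes as descriptive.

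This is a change of wording. It needs no further data or participants and leaves fewer tests to run. The cost is that within-arm p-values can no longer support statements about efficacy.
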